### Recruitment

Carefully selected recruiters, the VERITAS (Vaping Effects: Real-World International Surveillance) ambassadors (AB, [name], AM, KY, and MS), will make sure to identify and screen individuals for the VERITAS Cohort Study. The VERITAS ambassadors will pursue recruitment through social media channels, WhatsApp groups, Google email groups, posters in vape shops and universities, recommendations from other participants, and recommendations from local vape shop owners in each of the 6 geopolitical world regions (ie, Africa and Middle East, North America, Latin and South America, Asia-Pacific, Western Europe, and Eastern Europe). Ambassadors will instruct vape shop owners to ask their regular clients about their smoking history and EC use patterns to identify potential participants. The reference or control group will comprise adults who never used any tobacco or nicotine products. Control group participants will be recruited primarily among vaping individuals’ circles of friends and acquaintances. They will be matched for age and sex to the extent possible. In the event of shortfalls from this recruiting pathway, the Veritas Ambassadors will recruit further controls.

VERITAS ambassadors will be acting as the main point of contact for study participants and will be coordinated by a project leader ([name]). A document detailing the ambassadors’ roles can be found on the VERITAS Cohort website [33].

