All participants will then complete the Respiratory Symptom Experience Scale (RSES), a validated scale that asks participants to rate the frequency with which they experienced 5 respiratory symptoms in the past 30 days [35]. The 5 symptoms rated are as follows: (1) morning cough with phlegm or mucous, (2) coughing frequently throughout the day, (3) shortness of breath that makes it difficult to do normal daily activities, (4) becoming easily winded during normal daily activities, and (5) wheezing or whistling in the chest at times when not exercising or doing other physically strenuous daily activities. Rating for each symptom is made on a 5-point scale, where 1=Never (0 out of the last 30 days); 2=Rarely (1-5 days); 3=Occasionally (6-15 days); 4=Most days (16-29 days); 5=Every day (all 30 out of the last 30 days). A mean RSES score will be calculated by averaging the 5-item scores. The RSES can be found in the Multimedia Appendix 1.

Lastly, questions will assess participants’ sex, country of residence, employment status, highest educational attainment, height, and weight.

If necessary, surveys will be translated into the local language by the ambassador for countries where not all participants are fluent in English. Data will be collected on whether the participant completed the survey in English, Spanish (translation available on the platform), or their local language (in case it is determined that some questions of interest had some important difference in nuance when translated).

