### Statistical Analyses and Reporting

The primary objective of the study is to retrospectively estimate the effect of current, regular use of vaping products on respiratory symptom experience in the past 30 days, measured in this study by the mean score (0 to 5) on the 5-item RSES [35]. Details of sample size calculation and power analysis to detect differences in respiratory symptoms (ie, the RSES scores) between the “vapers cohort” and the “controls cohort” are included in Multimedia Appendix 1. In brief, with 75 participants per group, a study should be adequately powered to detect a difference of 0.57, the proposed minimal important difference, with a power of 98%. However, to detect a more conservative difference of 0.40, a study with 75 individuals per group would still have a power of 89%. The target study population will consist of approximately 500 exposed individuals and 250 matched controls–approximately 83 people who vape per each of the 6 world regions. If the initial recruitment falls short of the goal, or in the case of substantial early loss to follow-up, rolling enrollment will be considered to make up the deficit.

Data analysis of the RSES scores will be both descriptive and inferential in nature. The RSES scores and the demographic characteristics of the vapers cohort and the controls cohort will be descriptively summarized. We will test the null hypothesis that the RSES scores will not significantly differ between the vapers cohort and the controls cohort when adjusted for demographic differences. This hypothesis will be tested through a one-way between-subjects Analysis of Covariance in which the mean RSES score will be entered as the dependent variable, “Cohort” will be entered as the between-subjects independent variable, and 4 demographic variables—age, sex, education, and employment status—will be entered as covariates. Inferential and descriptive statistics will be reported for the Cohort variable adjusted for the effects of the covariates. *P* values <.05 will be considered statistically significant.

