Although this study promises important insights into respiratory symptoms and vaping behaviors among a culturally diverse group of adults who exclusively vape, it should be considered within the context of several limitations. First, its cross-sectional design limits the ability to draw conclusions about the causal relationship between vaping and respiratory symptoms. Longitudinal studies will be crucial to discern the prospective effects of vaping behavior on respiratory health. Second, the study’s reliance on nonprobability sampling methods may introduce a self-selection bias, impacting the generalizability of the findings to the broader population of exclusive vapers. However, given the rarity of this population subgroup, these methods were deemed the most practical approach to gathering a sufficient sample. Third, relying on a single respiratory health assessment (ie, RSES) based on self-report might introduce biases and inaccuracies. Participants might hesitate to disclose certain information or be influenced by social desirability bias, potentially affecting the data quality. Lastly, variations in survey interpretation due to linguistic, cultural, or regulatory differences across countries could lead to diverse responses, impacting the consistency and accuracy of the data collected for the research question.

The results obtained from the VERITAS study may offer crucial insights into the impact of vaping on health outcomes, providing a foundation for implementing essential public health measures. These findings can be effectively used within public health sectors and policies to address health concerns related to vaping, establishing necessary preventive measures to safeguard vulnerable populations. Moreover, the study methodology stands as a valuable reference for forthcoming research. Building such unique cohorts could serve as a pivotal resource for future studies, enabling the thorough examination of safety concerns and the quantification of potential risks or harm associated with vaping.

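### The primary ANCOVA leaves out region and survey language, though recruitment runs by region, controls are not matched on either, and the protocol says both may change answers

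*Protocol article*

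**What the plan says.** All references are to the protocol article.

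- **Primary model (Statistical Analyses and Reporting).** A "one-way between-subjects Analysis of Covariance in which the mean RSES score will be entered as the dependent variable". Cohort is the only factor, and "4 demographic variables—age, sex, education, and employment status—will be entered as covariates". The list is closed: it names no region, country or language term. For the test, P "values <.05 will be considered statistically significant".
- **Regions (same section).** The target is "approximately 83 people who vape per each of the 6 world regions". No regional target is stated for the 250 controls.
- **Source of controls (Recruitment).** Controls come mainly from the vapers' own social contacts and are matched on age and sex as far as can be managed. Region, country and language are not matching variables. There is a fallback: "In the event of shortfalls from this recruiting pathway, the Veritas Ambassadors will recruit further controls". No regional constraint is attached to it.
- **Language (Web-Based Survey Questionnaires).** Where needed, "surveys will be translated into the local language by the ambassador". The language of completion is recorded, in case wording turns out to carry a different nuance in translation. Country of residence is also recorded.
- **Acknowledged effect (Discussion).** Among the limitations, "variations in survey interpretation due to linguistic, cultural, or regulatory differences across countries could lead to diverse responses".

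**The concern.** This is a non-randomised comparison, so nothing in the design makes the two cohorts alike in region or language. The protocol builds region into recruitment, lets ambassadors produce translations of the instrument, records country and language, and says that these may move the answers. It then fixes a primary model without them.

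A factor that is related both to cohort membership and to the RSES score, and is left out of the model, shifts the estimated cohort difference. The shift can create a difference or hide one. Hiding one matters here because the hypothesis at the end of the Introduction is that vaping does not increase respiratory symptoms. If more controls than vapers came from a region with higher scores, vapers would look better than they should.

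**Working it through.** **1. The plan's own power figures, used only to obtain a plausible SD.** The text shown gives no SD and refers to the appendix. It says 75 per group can "detect a difference of 0.57, the proposed minimal important difference, with a power of 98" per cent, and gives 89% for a difference of 0.40. Solving SD = difference / [√(2/75) × (1.96 + z of the power)], two-sided:

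- 0.57 at 98%: SD = 0.87
- 0.40 at 89%: SD = 0.77

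No single SD returns both figures exactly as printed, but an SD of about 0.74 to 0.79 brings both within 2 percentage points. That is a separate matter. Here SD 0.77 to 0.87 is an assumed range.

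**2. Precision at the planned size.** SE = SD × √(1/500 + 1/250).

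- SD 0.77: SE = 0.060, so differences above 1.96 × 0.060 ≈ 0.12 are significant
- SD 0.87: SE = 0.067, so differences above about 0.13 are significant

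Small distortions can therefore affect the test, well below the 0.57 minimal important difference.

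**3. Size of the bias.** Suppose one region's mean RSES is shifted relative to the others, with no true cohort effect. Bias = (control share − vaper share in that region) × shift. Vapers spread evenly give 1/6 = 16.7% per region. The control shares and shifts are assumptions. The false-positive rate is P(|Z + bias/SE| > 1.96), with SD 0.77 (SE 0.0596).

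| Control share | Shift | Bias | Bias / SE | False-positive rate |
|---|---|---|---|---|
| 40% | 0.3 | (0.40 − 0.167) × 0.3 = 0.07 | 1.17 | about 22% |
| 30% | 0.2 | (0.30 − 0.167) × 0.2 = 0.027 | 0.45 | about 7% |

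Over a wider assumed range (SD 0.77 to 0.87):

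- a 10-point imbalance with a 0.20 shift gives a bias of 0.02 and a rate of about 6%
- 20 points with 0.40 gives 0.08 and 22 to 27%
- 30 points with 0.57 gives 0.17 and 72 to 82%
- if either the imbalance or the shift is zero, the bias is zero

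**4. Does adding region repair it?** Simulation with 2,000 runs, 500 against 250, six regions, SD 0.77 and no true cohort effect. Three regions score 0.40 higher; 50% of vapers and 30% of controls live there.

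| Scenario | Model | Mean bias | False-positive rate |
|---|---|---|---|
| Imbalance and regional shift | without region | 0.08 | 26% |
| Imbalance and regional shift | with region | 0.002 | 4% |
| Imbalance, no regional shift | either | 0.00 | about 5% |
| Balanced, regional shift | either | 0.00 | about 5.5% |

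The spread of the estimate in the first scenario was 0.0597 without region and 0.0593 with it.

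**The case against.** **The imbalance and the shift are both assumed.** This is correct. The document reports neither the regional make-up of the controls nor any RSES difference by region or language; the Discussion says only that responses could differ. A reader might infer that any imbalance in where controls were found biases the result. That is too strong: RSES must also differ by region or language after the four covariates.

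**Drawing controls from vapers' contacts tends to balance region and language.** This also stands in part. But it is only the main route, the fallback carries no regional constraint, and no balance check is stated.

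**The bias may be small.** A bias of 0.07 is about 12% of the minimal important difference (0.07 / 0.57), and the milder case raises the error rate only to about 7%. The planned decision, however, rests on P < .05, and a difference of 0.12 is enough to reach it.

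**The plan already deals with it.** Language is recorded, cross-country interpretation is a declared limitation, and further stratified analyses are allowed. Those analyses are optional and reported as descriptive summaries, so they do not adjust the primary comparison.

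**Timing.** A reader might also infer that controls answered later than vapers and that season distorts the comparison. The document does not support this. Further controls are recruited only if there is a shortfall, rolling enrollment is merely to be considered and applies to the study as a whole, and nothing shows that controls came later. No seasonal pattern in RSES is stated, and completion date is not listed among the variables collected.

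**Conclusion.** The point holds for region and survey language. The primary model excludes two recorded factors that the protocol itself treats as possible influences on the answers, in a non-randomised comparison whose controls are neither matched nor given a stated target on them. The covariate list is written out in full, so this is a stated choice and not a detail left open.

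The result is a risk of bias in either direction, not a demonstrated bias. Under the assumed inputs it runs from 0.027 (about 7% false positives) to 0.07 (about 22%), and is larger only under stronger assumptions. It rests on an SD back-solved from the power statement, on assumed regional shares and on assumed RSES shifts. No claim about calendar time is part of this conclusion.

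**What to change.** - Prespecify region (6 levels, derived from the recorded country of residence) and survey language (English / Spanish / other) as fixed factors in the primary ANCOVA, beside the four present covariates.
- Tabulate cohort by region and cohort by survey language, so that readers can see how balanced the cohorts are.
- If completion dates are available, examine them in a sensitivity analysis only.

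**Cost.** Region takes 5 and language 2 degrees of freedom, 7 in all, with about 748 participants enrolled. No new questionnaire items are needed. The SE may rise slightly if cohort and region are correlated. In the example with 40% against 16.7%, R² of cohort on region is about 0.065, so variance inflation is 1 / (1 − 0.065) ≈ 1.07. The 0.3 shift explains about 3% of the variance, so the SE changes by √(1.07 × 0.97) ≈ 1.02, a rise of about 2%. Region and language may overlap (for example Spanish with Latin and South America). That blurs their separate coefficients, but these are nuisance terms and are not to be interpreted.

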## Results

Participant recruitment started in April 2023, and enrollment was completed by November 2023 with 748 participants. Results will be reported in 2024.

## Discussion

Research into the respiratory health effects of regular vaping is limited [11,36,37]. Previous research investigating the health status of individuals who used to smoke faces challenges due to unknown health effects caused by prior smoking. Consequently, studies involving individuals who solely vape with no established smoking history are essential to identify potential harms attributed to vaping. A small prospective study of daily EC users who never smoked CCs demonstrated no significant alterations in lung function, inflammation, or structural abnormalities observed in lung scans [30]. Moreover, consistent respiratory symptoms were not reported in this study [30]. However, large longitudinal studies focusing on well-characterized EC users, with and without a history of CC smoking, are necessary to establish the long-term effects of regular vaping on respiratory health.

This proposed study aims to be the first investigation exploring the association between respiratory health effects and the use of ECs in a large group of individuals who exclusively vape, with no established CC smoking history. Additionally, the research will delve into potential confounding factors that could influence any association identified between vaping and respiratory symptoms.

Several noteworthy features distinguish this study. First, by enlisting participants globally, it intends to capture diverse experiences and behaviors related to EC use across different countries and regions. Second, the study’s focus on respiratory symptoms and in-depth characterization of vaping product use in a real-world context enhances its generalizability. Third, the study sample has been adequately powered to detect minimum clinically important differences in respiratory symptoms between exclusive vapers and those who neither vape nor smoke. Finally, the study implements a stringent 2-step verification process to deter potential abuse by unauthorized users attempting to exploit the possibility of receiving a gift card and uses manual analysis to identify and verify legitimate participants.

Although this study promises important insights into respiratory symptoms and vaping behaviors among a culturally diverse group of adults who exclusively vape, it should be considered within the context of several limitations. First, its cross-sectional design limits the ability to draw conclusions about the causal relationship between vaping and respiratory symptoms. Longitudinal studies will be crucial to discern the prospective effects of vaping behavior on respiratory health. Second, the study’s reliance on nonprobability sampling methods may introduce a self-selection bias, impacting the generalizability of the findings to the broader population of exclusive vapers. However, given the rarity of this population subgroup, these methods were deemed the most practical approach to gathering a sufficient sample. Third, relying on a single respiratory health assessment (ie, RSES) based on self-report might introduce biases and inaccuracies. Participants might hesitate to disclose certain information or be influenced by social desirability bias, potentially affecting the data quality. Lastly, variations in survey interpretation due to linguistic, cultural, or regulatory differences across countries could lead to diverse responses, impacting the consistency and accuracy of the data collected for the research question.

The results obtained from the VERITAS study may offer crucial insights into the impact of vaping on health outcomes, providing a foundation for implementing essential public health measures. These findings can be effectively used within public health sectors and policies to address health concerns related to vaping, establishing necessary preventive measures to safeguard vulnerable populations. Moreover, the study methodology stands as a valuable reference for forthcoming research. Building such unique cohorts could serve as a pivotal resource for future studies, enabling the thorough examination of safety concerns and the quantification of potential risks or harm associated with vaping.

## Appendix

Multimedia Appendix 1 Cohort study questionnaire.

## Abbreviations

CC: combustible cigarette
EC: electronic cigarette
PATH: Population Assessment of Tobacco and Health
RSES: Respiratory Symptom Experience Scale
VERITAS: Vaping Effects: Real-World International Surveillance
